# The efficacy of tourniquet assisted total knee arthroplasty on patient-reported and performance-based physical function: a randomized controlled trial protocol

**DOI:** 10.1186/1471-2474-15-110

**Published:** 2014-03-29

**Keywords:** Tourniquet, Total knee arthroplasty, Patient-reported, Performance-based, Physical function

## Abstract

**Background:**

Surgical treatment of osteoarthritis with total knee arthroplasty (TKA) usually takes place in a complete bloodless field using a tourniquet. However, doing the surgery without a tourniquet may reduce muscle damage, post-surgery pain and led to improved functional rehabilitation and mobilization.

**Methods/Design:**

A prospective, blinded, parallel-group, controlled superiority trial, with balanced randomization [1:1]. Patients aged 50 or older eligible for primary TKA for osteoarthritis will be consecutively recruited from Department of Orthopedic Surgery and Traumatology, Odense University Hospital, Denmark. A total of 80 patients will be randomly allocated to TKA with or without tourniquet application providing 40 patients for each of the two treatment arms. The tourniquet assisted TKA group will have an automatic, micro-processor-based pneumatic tourniquet inflated around the thigh during surgery. The non-tourniquet assisted TKA group will have surgery performed without application of a tourniquet. The primary aim is to compare tourniquet assisted to non-tourniquet assisted TKA on patient-reported physical function (KOOS-ADL). The secondary aim is to compare post-surgery pain, function in sports and recreation, quality of life, and performance-based physical function. The explorative outcomes include; use of pain medication, single-fiber muscle damage, and changes in mechanical muscle function. The primary endpoint will be at 3-months following surgical treatment, and the time-point for analysis of the primary outcome. However, follow-up will continue up to 1 year, and provide medium-term results. The treatment effect (difference in KOOS-ADL) will be analyzed using a random effects regression model, crude and adjusted results will be reported, if needed. Analyses will be based on the intention-to-treat (ITT). Subsequent per-protocol analysis may be necessary in the event of a substantial number of patients (> 15%) being lost during follow-up. The number needed to treat (NNT) for a positive effect of treatment (>10 points on KOOS-ADL) will be reported.

**Discussion:**

This is the first randomized clinical trial comparing the efficacy of tourniquet assisted TKA on patient-reported physical function supported by a range of performance-based secondary outcome measures. As such it will provide high quality evidence that may help determine whether tourniquet should be used in future TKA procedures in patients with osteoarthritis of the knee.

**Trial registration:**

ClinicalTrials
NCT01891266.

## Background

Osteoarthritis (OA) is the most common joint disease and a significant cause of morbidity in middle-aged and older populations
[1-3]. Knee OA is characterized by joint pain, swelling, reduced range of motion (ROM), decreased physical activity, and impaired quality of life
[4]. Following the development of OA, the associated pain and disability generally increase with time
[5,6]. In end-stage knee OA, total knee arthroplasty (TKA) may be the only effective treatment available to reduce pain and restore joint mobility and function.

TKA is an invasive procedure during which damaged cartilage is removed, joint deformities are corrected and the original knee joint is replaced with an artificial joint. The recovery period typically lasts for several months and patients often experience significant pain which may be only partly relieved by analgesia. Several factors such as the post-operative inflammatory response, muscle damage, pre-existing muscle weakness and swelling may contribute to the extensive recovery period. These factors may also negatively affect physical performance in the early post-surgery period.

Tourniquets inflated above systolic blood pressure have been used by surgeons for lower limb surgery for more than a century
[7-10] and are still the preferred method in elective TKA
[9,11-13]. The rationale for tourniquet use in TKA is primarily the optimization of intra-operative visibility and reduced blood loss
[9,12,14,15]. However, such benefits must be weighed against the potential complications which include; increased risk of direct vascular injury
[13,16], nerve palsy
[17-19], deep-vein thrombosis
[7,8,13,20] and subsequent pulmonary embolism
[7,21,22]. Additionally, acute pulmonary edema and cardiac arrest immediately following tourniquet release have been reported
[7,22,23]. There are also studies in the literature demonstrating that tourniquet use in TKA does not improve fixation
[24,25]. Tourniquet use may also affect a patients’ physical recovery since its use causes microscopic muscle damage, post-surgery swelling, pain, and reduced knee joint ROM
[7,24-28] and a greater understanding of patient-reported outcomes following TKA using a tourniquet is required. Furthermore, tourniquet use has been reported to cause post-surgery surface electromyography changes in the quadriceps muscles
[29], and has been associated with increased levels of myoglobin in plasma
[30], which collectively suggests pressure induced muscle damage does occur. Finally, patients undergoing non-tourniquet assisted TKA commenced rehabilitation exercises earlier and this may improve a patient confidence in using the new joint, decrease the incidence of complications associated with immobility and improve their overall satisfaction
[7,29]. The use of tourniquet for TKA is therefore controversial and well-designed randomized controlled trials are needed to provide high-level evidence to address these important issues. New trials should address aspects of recovery in physical function to fully capture the clinical implications of tourniquet use.

In response to the lack of high-level evidence the primary aim of this randomized trial is to assess the efficacy tourniquet assisted TKA on patient-reported physical function. The secondary aim is to compare post-surgery pain, function in sports and recreation, quality of life, and performance-based physical function. The explorative outcome measures include; use of pain medication, single-fiber muscle damage, and changes in mechanical muscle function. We hypothesize that non-tourniquet assisted TKA will result in superior patient-reported and physical performance-based outcome measures within the first 3-months compared with standard, tourniquet assisted, surgery.

## Methods/Design

### Study design

This trial will comply with CONSORT (Consolidated Standards of Reporting Trials) guidelines
[31,32], and has been designed as a prospective, blinded, parallel-group, superiority trial, with balanced randomization [1:1].

### Participants and recruitment procedures

Patients aged 50 years and older with an indication for TKA will be consecutively recruited from the Department of Orthopedic Surgery and Traumatology, Odense University Hospital, Denmark. The criteria for inclusion and exclusion are listed in Table 
1.

**Table 1 T1:** Criteria for participants in the study

**Inclusion criteria**	**Exclusion criteria**
Age > 50	Rheumatoid arthritis
	BMI > 35
Able to tolerate spinal anesthesia	Previous knee surgery
	Malignancy
Clinical and radiological knee OA according to the ‘Ahlbäck’ classification system	Muscle disease
	Deep vein thrombosis or other blood coagulation disorders.
	Neuromuscular problems
	Symptomatic bilateral OA, with planned surgery of the contra lateral knee within 1 year
	Decline or unable to participate

OA, Osteoarthritis; BMI, Body Mass Index.

On initial contact, patients will be evaluated by an orthopedic knee surgeon, who will establish the indication for surgery, and verify that all inclusion criteria and none of the exclusion criteria are met (Table 
1). Next, the patients will be invited to participate in the trial, and will receive verbal and written information about the trial in accordance with the information sheet approved by the ethics committee. Patients will be given the opportunity to ask questions about the trial and if they wish to participate they will complete a standardized consent form. Patients who do not wish to make a decision regarding participating in the trial during the consultation will be given a stamped addressed envelope and will be contacted by the research nurse no later than a few 4 after the consultation. The research nurse will also ensure that participants have signed the written consent form, are randomized and scheduled for the completion of all baseline measurements. Patients declining to participate in the trial will receive standard surgery (tourniquet-assisted TKA). An independent radiologist will stage the knee osteoarthritis severity using the Ahlbäck classification system
[33].

A compete overview of the recruitment procedures (enrolment, randomization, treatment allocation, follow-up and data analysis) is shown in Figure 
1.

**Figure 1 F1:**
[figure not shown]
Flow diagram through-out trial.

### Intervention

The entire surgical procedure will be performed under spinal analgesia with a typical duration of 60–90 min and all patients, regardless of length-of-surgery, will remain in the trial population. All patients will undergo surgery using a midline and a medial parapatellar incision through the joint capsule. Patients will receive a cemented total knee arthroplasty (P.F.C.® Sigma®, posterior cruciate retaining knee system, Depuy). Prior to surgery patients receive transexamic acid (Cyclocapron) to decrease bleeding. During surgery, pain management will consist of local infiltration anesthesia (300 mg naropin, 1 mg toradol and 0.5 mg epinephrine periarticularly). The post-surgery pain management will consist of paracetamol (1 g four times/day), contalgin (10 mg two times/day) according to our standard protocol and morphine analogs (10 mg Oxynorm) as required, with the aim of providing sufficient pain relief to facilitate early mobilization. Following discharge patients will receive one-week of anti-thrombosis treatment (fragmin, 5000 IE.sc). A single surgeon trained in surgery with and without the use of a tourniquet will perform both surgical procedures.

#### Group A: the tourniquet assisted TKA group

Patients in the tourniquet group will have surgery performed with an automatic, micro-processor-based pneumatic tourniquet (A.T.S. 2000 tourniquet system, Ref. 60-2000-101-00, Zimmer), patient-dependent size and inflated to 250 mmHg (± 3 mmHg pressure accuracy).

#### Group B: the non-tourniquet assisted TKA group

In the non-tourniquet assisted TKA group the entire operation will be performed without application of a tourniquet.

In-hospital rehabilitation will be standardized for both surgical treatments and consists of the use of crutches, range of motion and stair negotiation exercises all of which are performed under supervision of a physiotherapist. Duration of hospital stay is typically 2 to 3 days and patients are generally discharged with crutches. Following discharge the patients will be provided with a leaflet detailing exercises to continue at home as part of the ongoing rehabilitation process.

### Outcome measures

A single primary outcome measure was chosen to eliminate problems with result interpretation often associated with multiplicity of analysis
[34].

#### Primary outcome measure

##### The Knee injury and osteoarthritis outcome score (KOOS-ADL)

KOOS is patient-reported outcome measure with good evidence of reliability, validity and responsiveness in different population with varying pathologies, injury durations and activity levels
[35-37]. A 5-point Likert-scale is used and converted into a 100-point scale with zero indicating the worst possible health
[35].

#### Secondary outcome measures

Secondary outcomes include two patient-reported and physical performance-based measures:

##### The Knee injury and osteoarthritis outcome score (KOOS)

The remaining 4 subscales for pain, other symptoms, function in sport and recreation and knee-related quality of life.

##### Global perceived effect (GPE) score

Responsiveness is defined as the ability of a patient-reported outcome (PRO) instrument to detect changes over time in the construct to be measured
[38]. For evaluating responsiveness, a GPE score, where the patients rate their condition on a 7-point Likert-scale is a recommended responder criteria
[39]. The GPE questionnaire has the following seven response options: much better (3), better (2), somewhat better (1), no change (0), somewhat worse (−1), worse (−2) and much worse (−3). A 2-point change from ‘no change’ will be used as cut-off to categorize the response into: i) better, ii) no change, and iii) worse. At the 3-months and 12-months follow-up the patients will be asked to rate possible change in their condition from baseline.

##### Passive knee range of motion (kneeROM)

The number of degrees an examiner is able to move the knee joint through its full range of motion with no active effort from the patient. Mobility is measured in degrees using a standard (30 cm) goniometer
[40]. Inter-tester reliability (r = 0.98; ICC = 0.99) and validity (r = 0.97; ICC = 0.98) of goniometer measurements of knee joint motion have been shown
[41].

##### The 30-s chair-stand test (30-s CST)

The number of stands, from a seated position with arms folded across the chest, the patient is able to complete within a 30-second time period. CST measures lower-body strength and is an important aspect of fitness in older adults because of its role in common everyday activities. Past studies have shown that chair stand performance correlates well with laboratory measures of lower-body strength
[42], and with other indicators of interest such as walking speed, stair climbing ability and balance in older adults
[43]. CST has shown good intra- and inter-rater reliability in older adults with OA (ICC = 0.89)
[44,45].

##### 20 m self-paced and fast-paced walk test (20mWT)

The time in seconds required to walk a 20 m distance at self- and fast-pace. Walking time have been shown to be reliable (ICC = 0.93 and 0.98, respectively), and valid in reflecting functional performance in knee OA patients
[46]. Good agreement and excellent test-retest reliability have been demonstrated in both hip and knee OA patients
[44].

##### Timed up-and-go test (TUG)

The time in seconds needed for a patient to rise from an armchair, walk 3 m, turn, and then return to sit on the same chair. The TUG has been shown to be reliable and valid in reflecting performance-based test of mobility
[47,48], and activity in daily living evaluated by a patient-reported questionnaire
[49].

##### Self-reported pain intensity

Self-reported pain intensity is measured using the continuous (or “analogue”) aspect of the visual analogue scale (VAS), (0 = no pain and 100 = worst possible pain). The VAS scale is reliable and valid in assessing the intensity of musculoskeletal knee pain
[50].

#### Explorative outcomes

The explorative part of the trial investigates the changes in a range of muscle mechanical measurements; Isometric knee muscle strength (iMVC) during knee extension and flexion, leg extension power (LEP), rate of force development (RFD), force steadiness
[51,52], and surface electromyography (sEMG) supported by single-leg knee bending performance and muscle biopsies.

##### Maximal isometric knee strength

The maximal force (Nm) generated during isometric knee extension and knee flexion. Three consecutive test contractions will be performed, and the peak value will be selected for further analysis
[51]. The force-generating capacity is regarded as an essential functional outcome measure, and a prime factor to consider when examining functional limitations following TKA
[53]. A comparable isometric testing device has been shown to demonstrate discriminant validity and high test-retest reliability in knee OA patients
[54].

##### *Dynamic leg extension power* (LEP)

The maximal power (Watt; force x velocity) generated by the leg extensor muscles during ½-sec unilateral leg extension press in the Nottingham Power Rig. Each leg will be tested separately using 4–6 trial and separated by 30-s rest. Leg extension power has been described in detail
[55,56] and tested for reliability in patients with knee OA
[55].

##### The rate of force development (RFD_200_)

The change in force generated during the early phase of a muscle contraction (0-200 ms)
[52,57]. Several activities, such as descending stairs, fast-paced walking, or prevention of fall are characterized by a limited time to generate force, and the ability to rapidly produce force is an essential functional parameter
[2,58].

##### Force steadiness

The ability to produce a given force with a minimal amount of variation, and is routinely used to quantify mechanical and neuromuscular parameters in skeletal muscle
[52].

##### Surface Electromyography (sEMG)

The surface myoelectric (sEMG) signals associated with muscle contractions will be collected on lower limb muscles; m. rectus femoris, m. vastus medialis, m. vastus lateralis, m. biceps femoris and semitendinosus following the SENIAM guidelines
[59]. EMG will be collected during iMVC and force steadiness muscle contractions. (http://www.SENIAM.org). Good test-retest reliability was reported in healthy subjects
[60].

##### 30-s single-leg knee bending (30s-KneeBend)

The maximum number of bends completed within a 30 second time period. 30s-KneeBend measures the ability to execute fast stretch shortening cycles over the knee joint. The test is valid in discriminating between the symptomatic and the non-symptomatic leg in meniscectomized patients
[61] and moderate agreement and good test-retest reliability in patients with hip and knee OA has been reported
[44].

##### Single-fiber muscle damage

Muscle biopsy samples (2 × 100 mg) will be acquired during surgery in a subgroup of the patients (2 × 10). One sample will be collected prior to applying the tourniquet, and a second sample will be collected prior to the removal of the tourniquet. The muscle sample will be taken in every 4^th^ patient (e.g. patient no. 4, 8 and 12 etc.) Since the randomization sequence is concealed the unblinded surgeon will be responsible for selecting the next patient in line to ensure an equal distribution of samples drawn from each treatment group. The muscle biopsies will be performed through a small surgical incision into m. quadriceps femoris, and directly beneath the area where the tourniquet was applied. The muscle tissue samples will be frozen in liquid nitrogen, and saved for later analysis (single-fiber muscle isometric mechanical damage/function; force, force/cross sectional area, Ca^++^-sensitivity, and fiber stiffness).

### Adverse events

#### Surgery related data

A medical record audit will be performed at 3 month post-surgery where, surgery-time, intraoperative blood loss, wound infection, deep-vein thrombosis, pulmonary embolism, time-to-ambulation, prosthetic loosening, revisions will be reviewed and summarized. Also, the degree of knee varus/valgus before and after surgery will be evaluated.

#### Self-reported use of pain medication

The patient’s use of pain medication will be registered using a diary.

### Follow-up period

Assessments will be performed pre-surgery, 3, 14 days and 3, 6, 12-months after surgery with 3-months as the primary end-point. A summary of the outcome measures and time-points can be found in Table 
2.

**Table 2 T2:** Summary of outcome measures to be collected in the trial with time-points

**Primary outcome**	**Data collection instrument (unit)**	**Collection time-point**		
		**Baseline**	**Post (days)**	**Post (months)**
Function in daily living	KOOS	Pre	14	3,6,12
**Secondary outcome**				
KOOS - 4 subscales				
Pain	KOOS	Pre	14	3,6,12
Symptoms	KOOS	Pre	14	3,6,12
Sport and recreation	KOOS	Pre	14	3,6,12
Quality of life	KOOS	Pre	14	3,6,12
Questionnaire				
Global perceived effect	GPE			3,6,12
Bilateral physical Performance				
Knee range of motion (KneeROM)	Goniometer (°)	Pre	3,14	3,6
30-s chair-stand test (30s CRT)	(Number)	Pre	3,14	3,6
20-m self- and fast-paced walk test (20mWT)	Stopwatch (s)	Pre	3,14	3,6
Timed up-and-go test (TUG)	Stopwatch (s)	Pre	3,14	3,6
**Explorative outcomes**				
Mechanical muscle function				
Maximal isometric knee strength (iMVC)	Strain-gauge (Nm)	Pre		3,6
Dynamic leg extension power	(W)	Pre		3,6
Rate of force development (RFD)	(Nm/sec)	Pre		3,6
Surface electromyography (EMG)	Myon (mV)	Pre		3,6
Force steadiness	(Nm)	Pre		3,6
Unilateral physical performance				
30-s single-leg knee bending (30s-KneeBend)	(Number)	Pre		3,6
Pain				
Self-reported use of pain medication	(Quantity)	Pre	1-14	
Self-reported pain (VAS)	VAS	Pre	1-14	
Biopsies				
Muscle biopsy		Prior to applying and removal of the tourniquet		

### Statistical analysis

The primary statistical analysis will be performed on KOOS-ADL 3-month following surgery. To evaluate the treatment effect (mean difference in KOOS scores) we will employ a random or fixed effects linear regression model with point estimates
[62] and both crude and adjusted results will be reported. The regression model includes the interaction between treatment and elapsed time, adjusted for pre-surgery values and assumes data is missing completely at random (MCAR)
[62]. Model assumptions will be checked by residual plots. The secondary statistical analysis will include the same approach as described above for all the secondary outcomes. All analyses will be performed on the basis of intention-to-treat (ITT)
[63]. However, subsequent per-protocol analysis may be necessary in the event of a substantial number of patients (> 15%) being lost during follow-up. All data will be checked for Gaussian distribution and parametric statistics will be used were appropriate, otherwise non-parametric statistics will be applied. Finally, the number needed to treat (NNT) for a positive effect of treatment (>10 points on KOOS-ADL) will be analyzed. All statistical analyses are blinded and will be performed using Stata software (StataCorp, Texas, USA).

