[68]. Hence, to fully capture physical function in patients following joint replacement, performance-based testing should represent a variety of physical function domains (activity themes) representing the following five daily activities; *walking, sit-to-stand, ambulatory transitions, stair negotiation, and endurance*[45]. The current trial uses the 2×20 m fast-paced walk test, the 30-s chair-stand test, and the timed up-and-go test evaluate; walking, sit-to-stand, and ambulatory transition activity domains, repetitively. Despite the importance of also evaluating *stair negotiation activity,* no specific test is planned in the trial for two reasons. First, no recommendations about specific performance-based tests of physical function, with good measurement-property evidence (reliability, validity, responsiveness, and interpretability), is currently available. Second, the feasibility of stair negotiation tests is largely dependent on the environmental setting making them unsuitable for clinical trials at present
[45]. Likewise, no test for evaluating *endurance activity* has been planned for this trial due to the practical feasibilities issues associated with the six-minute walk test, e.g. patients are unable to walk for six minutes and exhausted following surgery. Further, endurance activity evaluation may be compromised in the early post-surgery phase since pain and swelling, rather than endurance, could limit patients’ performance. Consequently the current trial evaluates three primary activity themes using a core set of performance-based tests recommended by OARSI
[45], and from this core set of tests efficient comparisons of treatment outcomes across published literature can be made.

Evaluating the domain of pain or physical function in patients following joint replacement surgery is important
[39]. However, the decision to nominate physical function as primary outcome was due to two reasons. The KOOS questionnaire evaluates physical function in a variety of daily activities, and has an extensive subscale (KOOS-ADL, 17 items) devoted to evaluate physical function compared to the pain-subscale (KOOS-PS, 10 items). Additionally, WOMAC and KOOS are the most common PROs used to capture patient relevant information, relating to the impact of interventions in clinical research
[69]. WOMAC scores can subsequently be calculated based on data collected using the KOOS questionnaire, thus making efficient comparisons across published literature possible.

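### Missing completely at random is assumed for every outcome, but is implausible for the timed up-and-go and 20 m walk on days 3 and 14, where being unable to finish leaves no value

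*Protocol article*

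**What the plan says.** Under Statistical analysis, the protocol article describes the model for the treatment effect: "we will employ a random or fixed effects linear regression model with point estimates". It contains a treatment-by-time interaction, is adjusted for the pre-surgery value, and "assumes data is missing completely at random (MCAR". The assumption is then carried over: "The secondary statistical analysis will include the same approach as described above for all the secondary outcomes". The only stated response to substantial loss is that "subsequent per-protocol analysis may be necessary in the event of a substantial number of patients (> 15%) being lost during follow-up".

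The Follow-up period section sets the visits: "Assessments will be performed pre-surgery, 3, 14 days and 3, 6, 12-months after surgery with 3-months as the primary end-point". Table 2 places knee range of motion, the 30-s chair stand, the 20 m walk and the TUG at baseline, days 3 and 14, and months 3 and 6. Under Secondary outcome measures, the walk and the TUG are defined as times in seconds, the chair stand as a count, and knee range of motion as a passive measurement. The primary outcome, KOOS-ADL, is a questionnaire collected on day 14 but not on day 3.

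**The concern.** MCAR means that whether a value is missing is unrelated to anything about the patient, including how well the patient can move. For a timed mobility test within days of knee replacement that is hard to defend. Someone who cannot rise, walk 3 m and return has no time to record, and unless a rule says otherwise the result is blank.

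The article itself gives reasons to expect ability, and possibly arm, to matter. The Background links tourniquet use to pain, swelling and muscle damage, and says that patients operated on without one began rehabilitation exercises earlier. The Adverse events section audits time to ambulation. The stated hypothesis covers performance-based outcomes within the first 3 months, so days 3 and 14 lie inside it.

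At stake is the early performance comparison. If non-completers are mainly the slowest patients and are more common in one arm, the remaining patients no longer represent their arms.

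**Working it through.** **The plan's own figures.** None concerns missing early tests. The drop-out allowance (36 raised to 40 per group, 4/40 = 10%) belongs to KOOS-ADL. Every rate and effect below is therefore an assumption.

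**1. Completers only.** Let latent function be normal with SD 1 and higher values better. Patients below one common threshold cannot do the test. With proportions unable p_T (tourniquet) and p_N (none), and z = Φ⁻¹:

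- true difference d = z(p_T) − z(p_N)
- upward shift of an arm's mean when its lowest proportion p is removed: λ(p) = φ(z(p)) / (1 − p)
- completers-only difference = d + λ(p_N) − λ(p_T)

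| Unable, T vs N | d | λ(p_T) | λ(p_N) | Completers-only | Shrinkage |
|---|---|---|---|---|---|
| 20% vs 10% | −0.842 + 1.282 = 0.44 | 0.350 | 0.195 | 0.28 | 35% |
| 30% vs 15% | −0.524 + 1.036 = 0.51 | 0.497 | 0.274 | 0.29 | 43% |
| 40% vs 20% | −0.253 + 0.842 = 0.59 | 0.644 | 0.350 | 0.29 | 50% |

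**2. Lower rates.** With the same common threshold and true differences of 0.3 to 0.8 SD, the crude shrinkage is 16–19% at 5% missing overall, 26–28% at 10%, 34–36% at 15%, 40–41% at 20% and 49–51% at 30%.

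**3. The planned type of model.** This was simulated with 6,000 patients per arm, correlation 0.5 between visits, a random intercept, treatment by visit, and baseline adjustment. The true difference was 0.50 SD on days 3 and 14, and 20% were missing overall below a common threshold (by theory about 27% against 13%).

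- Crude difference by theory: 0.296, that is 1 − 0.296/0.50 = 41% too small.
- Mixed model: 0.356 (day 3) and 0.360 (day 14), about 28–29% too small.
- If missingness depends only on baseline, the mixed model gives 0.509 and 0.489. If day 14 is missing according to the observed day-3 value, it gives 0.493 at day 14, against 0.393 crude.

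Each is a single run, with a standard error for a crude difference of about √(2/6000) = 0.018. The model handles missing at random well. It recovers only part of the loss when inability itself causes the gap.

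**4. Direction.** With a true difference of 0.50 SD and 20% missing overall:

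- Lowest 20% missing in each arm: the shifts cancel, giving 0.50 (no bias).
- Lowest 40% missing in the non-tourniquet arm only: 0.50 + 0.644 = 1.14 (overstated).
- Lowest 40% missing in the tourniquet arm only: 0.50 − 0.644 = −0.14 (reversed).
- Best performers missing above a common threshold, for example because already discharged: 0.30 (by symmetry with the common lower threshold).

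**5. Later visits.** In the inability run of step 3, the mixed-model estimate for the same test at 3 months was 0.283 against a true 0.30.

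**The case against.** Several stronger readings are tempting, and the article does not support them.

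- *Early tests will be missing because patients cannot do them.* Nowhere is this stated, and no rate is given. The remark that "patients are unable to walk for six minutes and exhausted following surgery" explains why the six-minute walk was left out; the remark on pain and swelling in the early phase concerns endurance testing. Neither describes the TUG or the 20 m walk. They show awareness that early testing can fail for reasons of ability, no more.
- *Early differences are therefore understated.* This follows with a common ability threshold and a real difference between arms. Step 4 shows that the bias can be nil or reversed. The Intervention section gives a typical stay of 2 to 3 days, so fast recoverers may also miss day 3. That too departs from MCAR, but through a different group of patients.
- *All performance tests share the problem.* Knee range of motion is passive, and a chair-stand count has a natural value of 0.
- *The model can recover nothing.* It borrows from all of a patient's visits and recovers part of the loss. The 35–50% figures are for completers only.

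Two further objections have force. Relabelling MCAR as missing at random would not change a likelihood-based estimate, and would not cover inability, which is missing not at random. A scoring rule or reason code may also sit in a fuller document, so its absence from an article is not in itself a fault. What stands is that the article commits to MCAR for these outcomes, and that a per-protocol analysis above 15% loss does not address informative missingness.

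**Conclusion.** The point holds as a limited one. MCAR is a stated assumption, is stronger than a likelihood-based random-effects model needs, and is implausible for the TUG and 20 m walk on days 3 and 14. Those comparisons may be biased, most likely towards no difference if the slower-recovering arm has more non-completers. The size is unknown: 35–50% among completers under the assumed inability rates, and about 28–29% in a mixed model, against 41% crude, in the 20%-missing example. All of this rests on a normal latent scale, a sharp common threshold and assumed rates.

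A reader might infer that the main result is at risk. It is not: KOOS-ADL at 3 months is a questionnaire, not one of these timed tests. The point concerns secondary outcomes at early visits, but is worth settling before recruitment because the reason for a missed test may not be recoverable later.

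**What to change.** - Delete the MCAR statement. Name a likelihood-based random-effects model under missing at random as the main analysis; the Abstract already names random effects, whereas Statistical analysis leaves random or fixed open.
- At each performance visit, record 'unable to perform' separately from other reasons for a missed test, including discharge.
- Score the chair stand as 0 stands if the patient is unable.
- Prespecify a sensitivity analysis for the TUG and 20 m walk on days 3 and 14 that gives 'unable' the worst rank. Zero speed is an alternative for the walk only, since the TUG combines rising, walking, turning and sitting and has no natural speed. A rank-based comparison fits the article's existing provision for non-parametric methods; a cluster of zeros would fit a linear model poorly, which is why this should not replace the main analysis.
- Report the number unable by arm and visit.

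The cost is one case-report-form field and one extra analysis. Times in seconds remain the main reported scale.
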